### Sample size

Power Analysis and Sample Size (PASS, provided by Shanghai Datanine Software Co., Ltd., China) was used for sample size calculation. Based on prior studies and clinical experience, we expected the WOMAC total score to decrease by 17 points after acupuncture, a reduction by 13 points after diclofenac diethylammon gel, and a reduction by 10 points in the placebo group [32, 33]; the standard deviation is 10.24. The type I error inflation can be avoided by setting the significance level at 0.05 on a two-sided basis. Forty-two participants in each group will have 80% power to detect significant differences between the groups. The sample size was increased to 46 participants in each group to supplement for a possible 10% loss at follow-up. So, this trial will include 138 participants in total.

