### Primary outcome

The Western Ontario and McMaster Universities Osteoarthritis Index (WOMAC) [34] will be the primary outcome measure for this trial. The WOMAC is an osteoarthritis questionnaire with high reliability and validity that has been widely used in various clinical trials involving KOA patients [35]. WOMAC includes 5 pain-related items, 2 stiffness-related items, and 17 physical function-related items, each item is scored on a scale of 0–10, and the total score is on a scale of 0–240, with higher scores indicating more severe KOA symptoms in patients [36]. Outcome assessor will assess participants at baseline, week 4, week 8 and week 12, but the primary outcome will be the assessment at week 4.

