### Secondary outcomes

The WOMAC subscale (pain, stiffness, and physical function) at baseline, week 4, week 8, and week 12 and the total WOMAC scores at week 4 and week 8 will be used as secondary outcome indicators.Pain visual analog scale (VAS) [37]: Using a 100-mm horizontal line anchored by two descriptors, patients will determine the most relevant point for quantifying their pain intensity: a score of 0 represents “no pain” and a score of 100 represents “severe pain.” After randomization, VAS will be collected at baseline, week 4, week 8, and week 12.Arthritis Quality of Life Measurement Scale Simplified Scale (AIMS2-SF) [38] includes five dimensions of physical function, pain symptoms, influence, social interaction, and role components, with a total of 26 items, a scale of 1–5 is applied to each item, and the sum of all five dimensions represents the total score. After randomization, the AIMS2-SF will be collected at baseline, week 4, week 8, and week 12.Credibility/Expectancy Questionnaire [39] is a measure of treatment expectations and reasonable confidence for use in clinical outcome studies and it is only assessed once at the baseline.Emotional Monitoring: Patients with KOA are often accompanied by symptoms of anxiety and depression. In this trial, patients' emotional states will be assessed using the Beck Anxiety Inventory (BAI) [40] and Beck Depression Inventory (BDI) [41]. After randomization, BAI and BDI will be collected at baseline, week 4, week 8, and week 12.

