### Statistical analysis

The statistical analysis procedure of this trial will be performed using SPSS 22.0 software (IBM Corporation, Armonk, NY, USA). Statisticians responsible for data analysis will be independent of the research team and blind to the test settings. The data will be tested for normality using the quantile–quantile plots. We will analyze the data from WOMAC, VAS, AIMS2-SF, BAI, and BDI within the group and use paired-sample t-tests for those data that follow normal distributions, and in the case of data that did not conform to the normal distribution, Wilcoxon test will be used. Age, height, weight, and outcome assessments will be compared among the three groups, the one-way analysis of variance (ANOVA) will be applied to data conforming to a normal distribution, and the Kruskal–Wallis one-way ANOVA will be used to analyze data that do not follow a normal distribution. Intention-to-treat analysis will be used for outcome measurements to analyze missing values, based on the last observation carried forward method. In the analysis of missing values, only patients who attended at least 80% of the sessions and completed the follow-up in the allocated intervention group will be included. In addition, data will be tested by bilateral tests, and the confidence intervals are all 95% bilateral; *p* < 0.05 (*α* = 0.05) is considered to indicate statistical significance.

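### A two-sided 0.05 level does not prevent type I error inflation, and the stated tests never compare acupuncture with sham directly

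*Protocol article*

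**What the plan says.** On error control, the protocol article's Sample size section states that "The type I error inflation can be avoided by setting the significance level at 0.05 on a two-sided basis". It expects falls in WOMAC total as follows: "we expected the WOMAC total score to decrease by 17 points after acupuncture", "a reduction by 13 points after diclofenac diethylammon gel", and 10 points on placebo, with a standard deviation of 10.24. It claims 80% power at 42 per group for differences between the groups and names no pair.

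The Statistical analysis section names two kinds of test. Within groups it will "use paired-sample t-tests for those data that follow normal distributions", with Wilcoxon otherwise. Among the three groups, "the one-way analysis of variance (ANOVA) will be applied to data conforming to a normal distribution", with Kruskal–Wallis otherwise. For all of them p < 0.05 "is considered to indicate statistical significance". No pairwise contrast, testing order or adjustment is given.

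On the endpoint, the Primary outcome section lists assessments at baseline and weeks 4, 8 and 12, "but the primary outcome will be the assessment at week 4". The Secondary outcomes section then says that "the total WOMAC scores at week 4 and week 8 will be used as secondary outcome indicators".

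**The concern.** The Introduction asks whether acupuncture benefits patients with knee osteoarthritis. In this design that is the contrast of Group A with Group C. An omnibus test asks something else, namely whether any of the three means differ, and the gel alone can make it significant. A within-group test asks whether patients improved, which the plan already expects of the placebo arm.

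Two things are at stake. A significant primary p-value could be reported when acupuncture is no better than sham. And because the Sample size section declares inflation already dealt with, whoever analyses the trial has no reason to control error when moving from the omnibus result to pairs.

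A smaller fault sits beside this. Week-4 total WOMAC appears as both primary and secondary, while the week-12 total is collected but has no listed role.

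**Working it through.** **Inputs** (Sample size section): mean falls 17 (A), 13 (B), 10 (C); σ = 10.24; two-sided α = 0.05; n = 42 evaluable and 46 randomised per group. I take 10.24 as the SD of the quantity analysed; the article does not say whether it is the SD of change.

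**1. The plan's own figure.** For the one-way ANOVA, λ = nΣ(μᵢ − μ̄)²/σ². The grand mean is 13.33 and the squared deviations sum to 13.44 + 0.11 + 11.11 = 24.67. So λ = 42 × 24.67/104.86 = 9.88. With critical value F(0.95; 2, 123) = 3.07, power is 80.0%. At 41 per group it is 79.0%, so 42 is the smallest n that reaches 80%. The plan's figure is that of the omnibus test.

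**2. What omnibus rejection means if acupuncture equals sham.** Set A = C = 10 and let the gel be better by g. Then λ = 42 × (2g²/3)/104.86.

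| g (points) | λ | Omnibus rejects (n = 42) |
|---|---|---|
| 3 (plan's own gap, 13 − 10) | 2.40 | 26% |
| 5 (illustrative) | 6.68 | 62% |
| 7 (illustrative) | 13.08 | 90% |

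These rejections are correct, since the means do differ, but they say nothing in favour of acupuncture.

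**3. Family-wise error of the pairwise tests.** Three independent tests would give 1 − 0.95³ = 14.3%. The real contrasts share arms; simulation under equal means (n = 42, pooled variance) gives 12.1%. If pairs are examined only after a significant three-group ANOVA, the figure is 5.0%. With A = C and the gel better by 3, 5 or 7 points, a false A–C claim under that rule occurs in 3.8%, 4.7% and 5.0% of trials.

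**4. Power of the named contrasts.** The noncentrality is δ/(σ√(2/n)); at n = 42 the denominator is 10.24 × 0.2182 = 2.235.

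| Contrast | δ | Noncentrality, n = 42 | Power, n = 42 | Power, n = 46 |
|---|---|---|---|---|
| A vs C | 7 | 3.13 | 87% | 90% |
| A vs B | 4 | 1.79 | 42% | 46% |
| B vs C | 3 | 1.34 | 26–27% | 28–29% |

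The ranges reflect two-sample or pooled three-group degrees of freedom. If the omnibus test must also reject, A versus C is significant in 79% of trials at n = 42, so naming it directly gains about 8 percentage points.

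**5. The within-group test in the placebo arm.** If 10.24 is the SD of change, the noncentrality at n = 46 is 10/(10.24/√46) = 6.62 and power exceeds 99.99%. On that assumption a significant within-group result is expected under sham.

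**6. Options for the other two pairs once A versus C is significant** (simulation, planned means, n = 42):

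| Procedure after A vs C | A vs B significant | B vs C significant |
|---|---|---|
| A vs B, then B vs C | 41% | 5% |
| B vs C, then A vs B | 5% | 26% |
| Holm across the two | 32% | 19% |
| Both at 0.05 | 41% | 26% |

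The last row also holds 5% overall. If A and C truly differ, B cannot equal both, so at most one remaining null hypothesis is true. If A and C are equal, a false claim first requires a false A–C rejection (all three equal) or is that rejection itself (B different).

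**The case against.** The strongest reply is that design and analysis agree. The sample size reproduces exactly for the ANOVA, the Study design section states a three-way comparison, and the ANOVA holds 5% when all three arms are equal. Post hoc comparisons are also detail that a condensed article may leave to a full protocol or SAP not shown here. All of this stands, and a missing post hoc method alone would be no finding. But no unseen document can make the sentence on inflation true, and the tests and power that the article does state do not address the A–C question.

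A reader might go further than the text allows in four ways:

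- **That the trial runs at 12% family-wise error.** That rate belongs to pairwise tests done without a preceding ANOVA and without adjustment, which the plan does not state. It does not state the conditional rule that would hold 5% either.
- **That the omnibus test would mislead in 62% or 90% of trials.** Those figures need gel gaps of 5 or 7 points; the plan assumes 3, which gives 26%.
- **That within-group improvement is the planned evidence of efficacy.** The tests are listed, but no section gives them that role.
- **That the primary endpoint is in doubt.** The Abstract and the Primary outcome section both fix week 4; the secondary list is a slip to reconcile.

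**Conclusion.** The point holds in this form: the statement on error inflation is false, and the analysis as stated contains no test of acupuncture against sham. The sample size is not in error for the omnibus test, and that test keeps its level under the global null. The gap is one of interpretation: at the plan's own gel–placebo gap, about one trial in four would give a significant omnibus result with acupuncture equal to sham. Family-wise error on pairs could be 5% or about 12% depending on a rule the article leaves open while saying the matter is settled.

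The figures rest on normal data, a common SD of 10.24 for the analysed quantity, and 42 evaluable per group. The planned size already supports a properly defined A–C test.

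**What to change.** 1. Delete or correct the Sample size sentence on type I error inflation.
2. Name A versus C on change in week-4 WOMAC total, at two-sided 0.05, as the single primary test. Keep the omnibus test as descriptive.
3. Test A versus B and B versus C only after A versus C succeeds, by a procedure stated in advance. B versus C before A versus B, Holm across the two, or both at 0.05 would each control error. A strict sequence leaves whichever pair comes last significant in only about 5% of trials at the planned means. If A versus B comes first, the pair lost is B versus C, the check that the positive control works. State that both pairs have low power.
4. Say that the 80% power is that of the omnibus test, or replace it with the A–C figure (87% at 42 per group, 90% at 46).
5. Report within-group changes as means with 95% confidence intervals, as description only.
6. Reconcile the two outcome sections: week-4 total WOMAC primary only; weeks 8 and 12 secondary.

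The cost is wording, with no added patients. The small downside is that confirmatory claims on A versus B and B versus C depend on A versus C succeeding. The change should be dated before any outcome data are compared by group.

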### Randomization

In this trial, an independent researcher, who will not involve in any other trial procedures, will use a computer to create a random number list and then randomly assign eligible patients in a 1:1:1 ratio to one of the three groups. Sealable envelopes will be used for randomization allocation. The evaluator will inform the acupuncturists after the participant signs the informed consent form and completes the baseline assessments. The acupuncturists will open the envelope according to the participant’s screening sequence number and assign them to different groups to receive the intervention.

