### Study setting and recruitment

The trial will be conducted at the First Affiliated Hospital of Henan University of Chinese Medicine. The outpatient department of the hospital will recruit 138 KOA participants. The clinical research coordinator will perform a preliminary screening of participants and provide a detailed explanation to eligible participants in detail of the purpose of the study, and written informed consent will be obtained [30]. Afterward, the clinical assessor will conduct baseline assessments of participants who have obtained written informed consent. A randomization number will be assigned to each patient at enrollment, which is a unique direct identifier included on the case report forms (CRF).

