### Blinding

Acupuncturists cannot be blinded as they will be required to apply the various stimulation methods to intervene. However, there will be blinded of group assignments among the participants, because the acupuncture needles are the same, and the diclofenac diethylammon gel and placebo gel are identical in appearance. In addition, participants will be arranged in different rooms for treatment, in order to prevent them from communicating with each other to understand their treatment programs, and the acupuncturists will not communicate any information to participants about their treatment programs. Group assignments will be concealed from outcome assessor and data analysts. Only after data analysis, we will perform unblinding analysis. In the data summary stage, the three separation principles of researcher, operator, and statisticians will be implemented.

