### Group C

In the placebo group, subjects will be treated with sham acupuncture and placebo gel for 4 weeks. Sham acupuncture treatment procedure is the same as in Group B, and placebo gel will apply the same gel as in Group A.

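### Acupuncturists are unblinded to diclofenac versus placebo gel without need, and the envelope key (screening number) conflicts with the randomization number given at enrollment

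*Protocol article*

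**What the plan says.** **Allocation.** In the Randomization section, an independent researcher "will use a computer to create a random number list and then randomly assign eligible patients in a 1:1:1 ratio". The same section then has the acupuncturists open the envelope by the participant's "screening sequence number and assign them to different groups to receive the intervention". On timing it says: "The evaluator will inform the acupuncturists after the participant signs the informed consent form and completes the baseline assessments". The note under Table 1 likewise puts screening and consent ahead of assignment.

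**Patient number.** Study setting and recruitment says: "A randomization number will be assigned to each patient at enrollment".

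**Blinding.** The Blinding section says: "Acupuncturists cannot be blinded as they will be required to apply the various stimulation methods to intervene". It keeps the group from participants, the outcome assessor and the data analysts. It describes the two gels as looking the same, and it bars acupuncturists from telling participants about their treatment.

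**Interventions.** Group A has verum needling with placebo gel. Group B has sham needling with diclofenac gel. Group C has sham needling with placebo gel, and its section says: "Sham acupuncture treatment procedure is the same as in Group B".

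**Planned effects.** The Sample size section expects WOMAC total reductions of 17, 13 and 10 points in A, B and C, with SD 10.24.

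**The concern.** The reason given for unblinding the therapists does not cover everything they are told. Someone who needles must know whether to needle verum or sham. Nobody needs to know which gel accompanies sham needling in order to perform it. Yet opening an envelope that names the group reveals exactly that.

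At stake is the diclofenac-placebo contrast. A therapist in repeated contact with patients can convey expectation without stating anything, and the primary outcome is a questionnaire. The double-dummy design was chosen to equalise such influences, and the article's Discussion faults earlier trials for weak blinding.

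The second issue is operational. The article names two different numbers, issued at different points, and does not say how one maps to the other. A site could not tell from the text which number selects the envelope.

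**Working it through.** **1. What each arm reveals to the person needling** (Group A, B and C sections; Blinding)

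| | A | B | C |
|---|---|---|---|
| Needling | verum | sham | sham, same as B |
| Gel | placebo | diclofenac | placebo |
| Needling alone identifies the group | yes | no | no |

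With look-alike gels, nothing in the therapist's task separates B from C. Only the envelope does. In Group A the therapist can always infer the gel, because verum needling is paired only with placebo gel.

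**2. Size of the contrast exposed**

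The plan's own figure comes first. For a one-way ANOVA F test with means 17, 13 and 10, the grand mean is 13.33 and the squared deviations sum to 13.44 + 0.11 + 11.11 = 24.67. The noncentrality is n × 24.67 / 10.24². At n = 42 this is 42 × 24.67 / 104.86 = 9.88, and power at two-sided 0.05 is 0.800. The stated 42 per group reproduces. At 46 per group power is 0.838; after 10% loss (46 × 0.9 = 41.4) it is 0.794.

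The planned B-C difference is 13 − 10 = 3 points, and 3 / 10.24 = 0.29 SD. The standard error at 42 per group is 10.24 × √(2/42) = 2.23 points.

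The documents give no size for a therapist effect. As an assumption, suppose therapist knowledge shifts the B-C difference by 0.5, 1 or 1.5 points. That is 0.5/3 = 17%, 1/3 = 33% or 1.5/3 = 50% of the planned difference.

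**3. What the screening-number key could do**

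Assumptions, none stated in the article: screening numbers go to people who later fail, each failure skips an envelope, the list uses blocks of 6, and recruitment continues to 138. Results are from 6,000 simulated lists per failure rate; the power rows use a subset of 1,500.

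| Screen failures | 10% | 20% | 30% | 50% |
|---|---|---|---|---|
| Exact 46:46:46 | 5.9% | 3.1% | 2.0% | 1.1% |
| Mean gap, largest to smallest arm | 3.7 | 5.2 | 6.3 | 8.2 |
| 95th percentile of gap | 7 | 10 | 12 | 16 |
| Mean power after 10% loss | 0.794 | 0.793 | 0.793 | 0.792 |
| 5th percentile of power | 0.780 | 0.774 | 0.770 | 0.761 |

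The balanced reference is 0.794. Under simple randomization an exact split occurs in about 0.5% of trials with no failures at all (mean gap about 11), and failures add nothing.

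A separate scenario, which cannot occur together with the one above, is a list of exactly 138 envelopes with none added. Then 138 × (1 − failure rate) leaves about 124, 110, 97 or 69 randomized patients.

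**The case against.** The strongest reply is that the procedure is sounder than it looks.

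- **Disclosure before eligibility.** A reader might infer from the screening-number key that allocation is fixed and knowable before eligibility is settled, which would invite selective enrolment. The documents do not support this. Screening, consent and baseline precede assignment, and those assigned are "randomly assign eligible patients in a 1:1:1 ratio to one of the three groups". A coordinator screens and an assessor does the baseline work; the acupuncturist is brought in afterwards. A sealed list made in advance is normal, and nothing says anyone can see its contents early. This part of the reply stands.
- **Imbalance.** A reader might also infer that screen failures will break the 46:46:46 split. That needs a blocked list and screening numbers given to later failures, and the article states neither. Even then the imbalance is random, does not bias the comparison and costs almost no power. This stands too.
- **Who assigns.** One person generating the list while another opens the envelope is an ordinary division of tasks, loosely worded here.
- **Existing safeguards.** Acupuncturists are told to say nothing about treatment, and assessor and analysts are blinded. This reduces the risk but leaves unspoken expectation. The size of any therapist effect is unknown.
- **Condensed article.** Slip layout and tube coding may sit in a full protocol. But the article states that acupuncturists assign the groups and lists no information withheld from them, and the reason it gives does not reach B versus C.

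**Conclusion.** Two points hold.

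First, therapists are unblinded to diclofenac versus placebo in the sham groups without need. The stated rationale is correct for verum versus sham but incomplete, because it does not apply to B versus C. The contrast exposed has a planned difference of 3 points, or 0.29 SD. A therapist effect of a point or so would be a material share of it, though whether one would arise is an assumption.

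Second, the screening sequence number and the randomization number conflict and must be reconciled. The possible harm is loss of any blocking and skipped list positions. It is conditional on how screening numbers are issued, and small: mean power stays at 0.792 to 0.794 in the scenarios that recruit to 138. No early disclosure of allocation is shown.

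Both should be corrected, chiefly because of the first and because correction is cheap.

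**What to change.** 1. **Randomization.** Use the next sequential randomization number, and only once eligibility, consent and baseline assessment are complete. Have it released by the independent researcher already in the plan. Drop the screening number as the envelope key, so that this section agrees with Study setting and recruitment.
2. **Slip and supply.** Let the slip show only verum or sham needling plus a gel code. The pharmacy supplies active and placebo gel in identical coded tubes and holds the code list. The hospital's pharmacy department already makes the placebo gel.
3. **Blinding.** Reword along these lines: *acupuncturists know verum versus sham needling, but in the sham groups (B and C) are blind to whether the gel is active or placebo.* A blanket statement that they are blind to the gel would be false for Group A.

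**Cost.** A pharmacy code list and relabelling, with no extra patients. Trial status says recruitment had not begun. If patients have been enrolled since, the change applies to later ones only and should be documented.

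**Limit.** The diclofenac-placebo contrast gains most. The acupuncture-diclofenac contrast is only partly protected, because verum versus sham stays visible to therapists.
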